### Procedures

2.7

#### PROMBot-HSM-AF platform intervention

2.7.1

The research team will configure the PROMBot-HSM-AF chatbot and related remote monitoring platform, including definition of finite-state dialogue flows with AF-specific questions, message content, and input-validation rules. Pilot testing with 2–3 test users will also be conducted to identify usability issues and to verify delivery, latency, and data integrity. Health professionals involved in recruitment and follow-up will receive training on study procedures, including informed consent, platform registration, and use of the clinician interface to monitor incoming data.

Eligible patients undergoing AF ablation will be approached during their hospital stay. After receiving written study information, discussing questions, and providing informed consent, participants will complete a baseline assessment that will include demographics, medical history, recent clinical parameters (e.g., blood pressure and heart rate), and health-related quality of life (AFEQT, European Portuguese version) (13, 30). For participants randomized to the intervention group, PROMBot-HSM-AF will be set up before discharge by confirming WhatsApp is installed on the participant’s smartphone, registering the participant in the remote monitoring platform, linking their mobile number to PROMBot-HSM-AF, and sending a confirmatory message to verify correct enrollment. Patients (and caregivers, if applicable) will receive a brief demonstration and training, delivered by the study nurse, to ensure they can interact with the chatbot autonomously, and will also receive a leaflet with a brief explanation of the chatbot.

Participants in the intervention group will engage with PROMBot-HSM-AF via chatbot for 12 weeks. The chatbot will request self-reported health metrics (e.g., body mass, blood pressure, heart rate, step count, AF-related symptoms) and general well-being, supplemented with brief educational prompts (31). Participants who do not already own a validated blood pressure monitor will be provided with one at enrollment; device ownership is assessed during the baseline visit.

In the first month, chatbot interactions will occur daily, focusing on post-ablation symptom surveillance and medication adherence. After that, the cadence will taper to reduce burden in later weeks while maintaining essential monitoring. Chatbot prompts will remain open for 24 h, after which nonresponses will be recorded as missing data. A study nurse or physician will review patient entries weekly and may proactively contact participants reporting concerning symptoms or lapses in engagement. PROMBot-HSM-AF will not replace routine follow-up; all patients will continue standard clinical care, with chatbot data available to the study clinical team to complement or inform consultations at the treating cardiologist’s discretion.

At the end of the 3-month follow-up period, all participants will undergo post-intervention assessments during a routine hospital visit. If necessary, these assessments will be conducted via secure videoconference. The PROMs will focus on the effect of AF on health-related quality of life. Participants in the intervention group will also complete validated measures of usability and perceived usefulness. They will also take part in a brief semi-structured interview to share their experience of using the chatbot. Semi-structured interviews will also be conducted with healthcare professionals directly involved in patient care (e.g., cardiologists, nurses, and technicians). These interviews are intended to elicit qualitative insights regarding their experience with the chatbot-based intervention, as well as their perceptions of its usability, clinical relevance, and impact on workflow integration.

#### Control group

2.7.2

Participants allocated to the control group receive standard post-ablation care as delivered at Santa Marta Hospital, which includes structured discharge instructions with written educational materials about post-ablation care, scheduled follow-up appointments at 1 month and 3 months post-discharge, open access to the cardiology clinic telephone line during working hours for clinical concerns, and a 24-h hospital telephone service for urgent medical issues. Control group participants do not receive remote monitoring between scheduled appointments.

Both intervention and control groups complete identical standardized assessments at baseline (pre-discharge) and 3 months post-ablation. The timing of data collection activities is outlined in Table 1.

**Table 1 T1:** Schedule of enrollment, interventions, and assessments for the PROMBot-HSM-AF trial.

TRIAL PERIOD		Enrollment	Post-randomization				
Timepoint	Arm	⩽ day 0	Day 0	M1	M2	M3	M12
Target window		up to day 0	day 0	30±3 d	60±5 d	90±5 d	365±14 d
ENROLLMENT							
Eligibility screen	I+C	X					
Informed consent	I+C	X					
Randomization/allocation	I+C		X				
INTERVENTIONS							
PROMBot-HSM-AF	I			X	X	X	
Standard care	C		X	X	X	X	
PRIMARY OUTCOMES (FEASIBILITY)							
Recruitment rate	I+C	X	X				
Retention rate	I+C					X	
Engagement rate	I			X	X	X	
BASELINE CHARACTERISTICS							
Demographics	I+C		X				
AF history & comorbidities	I+C		X				
Procedure-related characteristics	I+C		X				
CLINICAL OUTCOMES (HOSPITAL-REPORTED)							
AF recurrence (AAD/cardioversion/repeat ablation)	I+C			X	X	X	X
Complications (readmission, ED visit, thromboembolism, major bleeding, tamponade)	I+C			X	X	X	X
All-cause mortality	I+C						X
Cardiology/internal-medicine consultations	I+C					X	X
Diagnostic tests (ECG, Holter)	I+C			X	X	X	X
PROMs							
AFEQT	I+C		X			X	
ESC quality-indicator items (weekly, rotating)	I			X	X	X	
Symptom checklist	I			X	X	X	
Medication adherence	I			X	X	X	
BIOSIGNALS							
Body mass	I			X	X	X	
Blood pressure	I			X	X	X	
Heart rate	I			X	X	X	
Step count	I			X	X	X	
ACCEPTABILITY & USABILITY							
Patient experience (SUS, PSSUQ, interview)	I					X	
Healthcare-professional experience (SUS, PSSUQ, interview)	HCP					X	

The schedule follows the SPIRIT figure convention (34).

M, month; d, days. Arm: I = intervention; C = control; HCP = healthcare professionals.

#### Clinical monitoring interface

2.7.3

Healthcare professionals access patient data through a secure web-based clinical monitoring interface integrated with the hospital’s electronic health record system. The interface provides real-time visualization of patient-reported data with trend graphs, automated alerts for concerning values, patient engagement metrics, and summaries of symptom reports.

A designated study nurse reviews the interface weekly during routine working hours. The clinical team maintains 24-h access for clinical decision-making purposes. All access is logged for audit purposes.

#### Safety monitoring protocol

2.7.4

Automated alerts are generated when patient-reported values exceed predefined clinical thresholds or when concerning symptom patterns are identified. Alert thresholds are defined as follows:

**Critical alerts (immediate response required):** Systolic blood pressure ⩾180 mmHg or less than 90 mmHg; diastolic blood pressure greater than 110 mmHg or less than 60 mmHg (32, 33); heart rate greater than 120 bpm or less than 50 bpm (29); new onset chest pain, syncope, or severe dyspnea; or three consecutive missed responses indicating potential disengagement.

**Response protocol for critical alerts:** The study nurse contacts the participant by telephone within 1 h during working hours or within 4 h outside working hours. For immediately life-threatening symptoms (e.g., chest pain suggestive of acute coronary syndrome, syncope), participants are advised to contact emergency medical services. Before escalation, the nurse verifies implausible values with the participant (confirming the technique and requesting a repeat reading) to exclude measurement error, escalating conservatively where uncertainty persists. For other concerning values, the study nurse coordinates with the treating cardiologist to determine appropriate clinical action, which may include scheduling an urgent clinic appointment, ordering diagnostic tests, or adjusting medications.

**Warning alerts (review within 24 h):** Systolic blood pressure 160 to 179 mmHg or diastolic blood pressure 100 to 109 mmHg on two or more occasions(32); heart rate 100 to 119 bpm or 50 to 60 bpm on two or more occasions(29); or reported worsening of existing symptoms.

All alerts and clinical actions taken in response are documented in both the study database and the participant’s electronic health record. Participants receive clear written instructions at enrollment specifying symptoms requiring immediate emergency medical attention vs. those that can be reported through the chatbot for routine clinical follow-up.

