#### Patient-reported outcomes and biosignals

2.9.4

Health-related quality of life will be assessed using the AFEQT, a validated, disease-specific instrument for AF (38). The AFEQT comprises 20 items across four domains (Symptoms, Daily Activities, Treatment Concerns, and Treatment Satisfaction) with an overall score (0–100) derived from the first three domains; higher scores indicate better quality of life. A change of ⩾5 points is generally considered clinically meaningful (13). The AFEQT will be administered at baseline and follow-up to assess changes in AF-related symptoms and the broader impact of management strategies on daily life. To complement the AFEQT, participants will complete brief, rotating weekly questions aligned with the ESC quality of treatment indicators (31), assessing symptom status, physical functioning, emotional well-being, cognitive function, and knowledge of AF-related risk factors. Each question will be administered once per week to minimize participant burden.

All PROMs and biosignals will be collected via the chatbot. Body mass, blood pressure, and heart rate will be self-reported daily for the first four weeks and weekly thereafter, with blood pressure and heart rate measured using a blood pressure monitor. Physical activity will be tracked as daily step counts via the smartphone pedometer. Symptoms, including palpitations, dyspnea, chest pain, dizziness/syncope, fatigue, puncture-site changes, and edema, will also be reported daily during the first four weeks and weekly thereafter. To mitigate self-report bias, participants receive standardized training on device use and measurement technique at enrollment.

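### A diastolic pressure of exactly 110 mmHg or a heart rate of exactly 120 bpm raises neither a critical nor a warning alert, although lower repeated readings do

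*Protocol article*

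**What the plan says.** Section 2.7.4 of the protocol article defines two tiers of automated alert.

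- **Critical.** Diastolic pressure: "diastolic blood pressure greater than 110 mmHg or less than 60 mmHg". Heart rate: "heart rate greater than 120 bpm or less than 50 bpm". Systolic pressure: "Systolic blood pressure ⩾180 mmHg or less than 90 mmHg". The nurse telephones within 1 h in working hours or within 4 h outside them.
- **Warning, reviewed within 24 h.** Diastolic pressure: "diastolic blood pressure 100 to 109 mmHg on two or more occasions". Heart rate: "heart rate 100 to 119 bpm or 50 to 60 bpm on two or more occasions". The systolic band reads "Systolic blood pressure 160 to 179 mmHg".

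Without an alert, the scheduled human check is the one in section 2.7.1: "A study nurse or physician will review patient entries weekly". Section 2.9.4 sets the reporting frequency: "Body mass, blood pressure, and heart rate will be self-reported daily for the first four weeks and weekly thereafter".

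**The concern.** A two-tier alert rule should never be silent on a value that is worse than one it warns about. Here the upper critical limits for diastolic pressure and heart rate are strict inequalities, while the warning bands end one unit below the same numbers. One integer on each scale is left without a tier.

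These are the stated definitions for an automated rule, and software applies inequalities literally. If the rule is coded as written, a participant without alert-triggering symptoms who keeps reporting 110 mmHg or 120 bpm sets off neither the telephone contact nor the 24 h review. The values remain visible on the clinical interface but may wait for the weekly check. A fast heart rate is directly relevant after AF ablation. The Discussion also offers these safety procedures as a possible template for similar interventions, so the thresholds may be copied.

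**Working it through.** **1. Classify every integer by the section 2.7.4 rules.**

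| Measure | Warning (two or more occasions) | No tier | Critical |
|---|---|---|---|
| Systolic, 160 and above | 160–179 | none | 180 and above |
| Diastolic, 100 and above | 100–109 | **110** | 111 and above |
| Heart rate, 100 and above | 100–119 | **120** | 121 and above |
| Heart rate, 60 and below | 50–60 | none | below 50 |

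No other section of the article assigns 110 mmHg or 120 bpm to a tier.

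**2. Run short sequences through the rule.**

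| Diastolic readings | Result | Heart-rate readings | Result |
|---|---|---|---|
| 100, 100 | warning | 100, 100 | warning |
| 109, 109 | warning | 119, 119 | warning |
| 109, 110 | none | 119, 120 | none |
| 110, 110, 110 | none | 120, 120, 120 | none |
| 111 | critical | 121 | critical |

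The second reading in 109, 110 does not count as a second warning occasion, so a worsening pair is treated more leniently than a stable one.

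**3. Scheduled exposure.** Daily reporting for four weeks gives 28 readings. Weekly reporting for the remaining eight of the 12 weeks gives 8. So 28 + 8 = 36 readings per participant, and 36 × 38 intervention participants = 1,368 readings of each measure.

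**4. Expected readings at the gap value.** The article gives no distribution, so normality and the means and SDs below are assumptions. For gap value v:

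expected count = 1,368 × [Φ((v + 0.5 − mean)/SD) − Φ((v − 0.5 − mean)/SD)]

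| Measure | Mean, SD | Expected readings at the gap |
|---|---|---|
| Diastolic, v = 110 | 75, 8 | 0.005 |
| | 80, 10 | 0.61 |
| | 85, 12 | 5.2 |
| Heart rate, v = 120 | 70, 10 | under 0.001 |
| | 75, 15 | 0.40 |
| | 80, 20 | 3.7 |

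**5. Check the repair.** With critical at diastolic ⩾110 and heart rate ⩾120, the bands become 100–109 then 110 and above, and 100–119 then 120 and above. No gap remains in either upper range.

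**The case against.** The strongest reply concerns weight, not fact. Counting readings overstates the problem, because what matters is a participant with a gap reading and no other numeric alert. Section 2.7.4 sets no time window for two or more occasions, so over 36 readings someone who reaches 110 or 120 will usually also have two warning readings or a critical one.

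A simulation under the same normal assumptions, with the between-person share of variance assumed to be 0, 0.5 or 0.8, supports this. It counts participants with a gap reading and no high-side alert on that measure at any time:

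- Diastolic, mean 85 and SD 12: about 0.39, 0.17 and 0.01 participants in the whole trial.
- Heart rate, mean 80 and SD 20: about 0.05, 0.05 and 0.002.
- The highest value in any scenario is a little under 0.5 (diastolic, mean 80 and SD 10, independent readings), falling to 0.06 at a share of 0.5.
- Repeated gap readings with no such alert: at most 0.03 participants.

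Other safeguards also exist: symptom alerts, 24-h access to the interface by the clinical team, and the telephone lines of standard care. The deployed code is not visible, and the cited sources may support strict limits, in which case the slip lies at the top of the warning bands.

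Much of this stands. The expected effect is small, and the documents cannot settle which edge is wrong. Two limits apply. The other alert may come well before or after the gap reading. Self-reported values may also be rounded, and 110 and 120 are round numbers, so the counts could be higher than a smooth normal curve suggests. None of the reply makes the rule correct as written.

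**Conclusion.** The concern holds. As written, exactly 110 mmHg diastolic and exactly 120 bpm belong to no tier, while repeated lower readings warn and readings one unit higher are critical. The contiguous systolic and low heart-rate bands in the same section suggest a drafting slip, though intent cannot be proved from the text.

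The size is one integer per measure. Under the stated assumptions that is at most about 5 diastolic and 4 heart-rate readings in the trial, with fewer than one participant expected to go without any other high-side alert on that measure. It is a defect in a participant-safety rule that should be fixed. It does not touch the primary feasibility outcomes, and certainty extends to the published wording only, not to the deployed code.

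**What to change.** Make the bands contiguous in both the protocol and the alert code. The simplest form is critical at diastolic ⩾110 mmHg and heart rate ⩾120 bpm, matching the systolic form. The alternative is to keep the strict critical limits and extend the warning bands to 110 mmHg and 120 bpm. The first option puts the boundary values in the telephone-contact tier, so the clinical team should choose.

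Then test the deployed rule with diastolic 109, 110 and 111 and heart rate 119, 120 and 121, single and repeated. If the code already handles these values, only the published text needs correcting.

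The cost is a one-symbol or one-digit edit per threshold and a short boundary test. By the range above, the first option adds at most about 5 diastolic and 4 heart-rate critical alerts over the whole trial.

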### Technical description of the chatbot

2.8

The PROMBot-HSM-AF chatbot is a rule-based, finite-state-machine chatbot delivered via WhatsApp, supporting numeric, multi-choice and free-text inputs with branching and input-validation rules. Unlike standard follow-up, it enables structured, time-stamped collection of PROMs and self-measured physiological data between clinic visits, with conditional follow-up questionnaires triggered by specific symptoms to provide clinicians with additional detail. Collected measures, their frequency, and timing are detailed in Table 1 (34); Figure 2 illustrates an example WhatsApp conversation flow. The chatbot operates in European Portuguese, with screenshots shown in English for illustrative purposes; technical terminology (e.g., systolic/diastolic blood pressure) is explained in plain language during patient training at enrollment. Full implementation details are provided in our previously published work (35).

**Figure 2 F2:**
[figure not shown]
Example screenshots of the PROMBot-HSM-AF interface.

### Outcome measures

2.9

Data from participating patients will be systematically collected and analyzed to evaluate predefined study outcomes. Outcomes are organized as a single set of primary feasibility outcomes and several sets of secondary or exploratory outcomes grouped by data type and source; baseline variables are reported as descriptors. The study arm and timepoints for every measure are summarized in Table 1.

#### Primary outcomes (feasibility)

2.9.1

The primary outcomes of this trial are feasibility parameters, including recruitment rate (eligible patients providing consent), retention rate (participants completing the 3-month follow-up), and engagement rate (proportion of chatbot prompts answered within 24 h) (36, 37).

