**Methods and analysis:**

PROMBot-HSM-AF is a single-center, open-label, randomized controlled pilot (feasibility) trial with two parallel groups, conducted at Santa Marta Hospital, Lisbon, Portugal. Seventy-six patients undergoing AF ablation will be randomized in a 1:1 ratio to either chatbot-supported follow-up or standard care. The primary feasibility parameters are: recruitment rate (proportion of eligible patients consenting), retention rate at 3 months, and chatbot engagement rate (proportion of chatbot prompts answered). Acceptability and usability will be assessed using behavioral indicators (engagement and retention), the System Usability Scale (SUS), the Post-Study System Usability Questionnaire (PSSUQ), and semi-structured interviews with patients and healthcare professionals. Quantitative data will be analyzed descriptively with exploratory between-group comparisons. Semi-structured interviews with patients and healthcare professionals will be analyzed using thematic content analysis.

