The primary objective of this pilot study is to evaluate the feasibility and acceptability of integrating PROMBot-HSM-AF, a chatbot-based platform for collecting PROMs and clinical parameters, into routine post-ablation follow-up care at a tertiary hospital. The specific aims, framed for the feasibility and pilot phase, are to: (1) quantify recruitment, retention, and engagement rates over the 3-month follow-up and compare each against pre-specified progression thresholds (retention ⩾80%, engagement ⩾70%), constituting the primary outcomes; and, as secondary, exploratory outcomes, (2) assess the usability and acceptability of the chatbot (patients) and of the clinical monitoring interface (healthcare professionals) at 3 months, using validated usability measures (System Usability Scale [SUS], Post-Study System Usability Questionnaire [PSSUQ]), behavioral indicators, and semi-structured interviews; and (3) evaluate the preliminary integration and data completeness of PROMs (e.g., Atrial Fibrillation Effect on Quality-of-Life [AFEQT]) collected via the platform over the 3-month follow-up, and explore between-group differences as hypothesis-generating estimates to inform a definitive trial.

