#### Inclusion criteria

2.3.1

Patients are eligible for enrollment if they meet all of the following criteria:
Age 18 years or older;Documented diagnosis of paroxysmal or persistent AF based on clinical assessment and coded according to the International Classification of Diseases, 11th Revision;Undergone catheter ablation for AF at Santa Marta Hospital during the study recruitment period;Able to use the PROMBot-HSM-AF chatbot independently or with caregiver assistance (Portuguese literacy sufficient to follow instructions and ability to operate a smartphone); digital literacy is assessed individually, with caregiver-assisted enrollment available for older adults willing to learn;Clinically stable at discharge, defined as absence of any complication requiring continued inpatient care or urgent reintervention (e.g., cardiac tamponade, major access-site bleeding, high-grade atrioventricular block); minor, self-limiting findings (e.g., uncomplicated groin haematoma) do not preclude participation;Provision of written informed consent.

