#### Exclusion criteria

2.3.2

Patients are excluded if they meet any of the following criteria:
Severe cognitive impairment preventing comprehension of study procedures, such as moderate-to-severe dementia or other neurological conditions limiting capacity to consent;Severe uncorrected visual impairment or motor disability preventing smartphone operation even with caregiver support;Explicit refusal to use digital technology or unwillingness to share health data required for the study;Clinical or contextual conditions rendering 3-month follow-up unfeasible, including anticipated relocation outside the hospital catchment area or concurrent participation in another interventional study with overlapping endpoints;Life expectancy less than 6 months.

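### The recruitment rate overstates uptake, because refusing digital technology or data sharing counts as ineligibility and leaves the denominator

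*Protocol article*

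**What the plan says.** The Protocol article defines the outcome twice. Section 2.9.1 gives "recruitment rate (eligible patients providing consent" and the Abstract gives "recruitment rate (proportion of eligible patients consenting". Both make eligible patients the denominator.

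Who is eligible is set in sections 2.3.1 and 2.3.2:

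- Section 2.3.1 opens with "Patients are eligible for enrollment if they meet all of the following criteria", and the last item on its list is "Provision of written informed consent".
- Section 2.3.2 excludes patients for "Explicit refusal to use digital technology or unwillingness to share health data required for the study".

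Section 2.7.1 uses the word differently: "Eligible patients undergoing AF ablation will be approached during their hospital stay". Information and consent come after that step. Table 1 also has separate rows for the eligibility screen and for informed consent.

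The last paragraph of the Introduction says that recruitment, retention and engagement will be quantified, and that the trial will "compare each against pre-specified progression thresholds". The thresholds listed are 80% for retention and 70% for engagement. Section 2.4 sizes the trial on those two rates. Neither place gives a figure for recruitment.

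**The concern.** A recruitment rate should show how many of the patients who could take part agree to do so. Not wanting the technology, or not wanting to send health data through it, is an obvious reason to decline a trial of a WhatsApp chatbot that collects such data. Section 2.3.2 moves exactly these patients from declined to ineligible, so the rate describes uptake only among those who have not objected to the intervention.

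Such a refusal will usually surface when the patient is approached. The same answer could then be logged as an exclusion or as declined consent, and the article gives no rule for choosing. The use of *eligible* both before consent (section 2.7.1) and including consent (section 2.3.1) adds to the uncertainty.

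Two things are at stake. The first is accrual planning for the multi-centre trial that the Discussion says will follow if the feasibility criteria are met. The second is the Discussion's claim that success criteria were explicitly set in advance, which is not true of recruitment.

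**Working it through.** The article states no expected value, threshold or sample size for the recruitment rate, so there is no figure to reproduce. The check is ratio algebra.

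**Definitions**

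- N = patients who meet every criterion apart from consent and the refusal exclusion in section 2.3.2.
- d = share of N removed for refusing digital technology or data sharing.
- c = share of the remaining patients who consent.

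The documents give neither d nor c, so the values below are assumptions.

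**Formulas**

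- Consenting patients = N(1 − d)c.
- Rate when refusers are excluded (section 2.3.2, with eligibility before consent as in section 2.7.1) = N(1 − d)c / [N(1 − d)] = c.
- Uptake among all otherwise eligible patients = N(1 − d)c / N = (1 − d)c.
- Inflation factor = c / [(1 − d)c] = 1/(1 − d), whatever the value of c.

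**Results**

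| Assumed d | Inflation 1/(1 − d) | Uptake if c = 50% | Uptake if c = 70% | Uptake if c = 90% |
|---|---|---|---|---|
| 0.1 | 1/0.9 = 1.11 | 45% | 63% | 81% |
| 0.2 | 1/0.8 = 1.25 | 40% | 56% | 72% |
| 0.3 | 1/0.7 = 1.43 | 35% | 49% | 63% |

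In each column the rate reported under the plan is c itself: 50%, 70% or 90%.

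**Effect on accrual, at d = 0.3 and c = 0.7**

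- The reported rate is 70%; uptake is 0.7 × 0.7 = 49%.
- The target of 76 patients (section 2.4) needs 76/0.49 = about 155 otherwise eligible patients.
- Someone who took the 70% as uptake in that population would expect 76/0.70 = about 109.

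**Effect of the missing logging rule.** With the same patients, the reported rate is 70% if every such refusal is logged as an exclusion and 49% if every one is logged as declined consent. Mixed logging falls between the two.

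**Thresholds.** Three rates are said to be compared with pre-specified thresholds; two thresholds are given. The statement cannot be carried out for recruitment.

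**The case against.** A reader might infer that the rate is 100% by construction, since section 2.3.1 makes consent a condition of eligibility, and that the outcome can therefore show nothing. The documents do not support this. Section 2.7.1 calls patients eligible before they are approached, Table 1 separates screening from consent, and the Abstract's wording presupposes eligible patients who do not consent. Listing consent among inclusion criteria is common form. Patients who decline because of randomisation, time or lack of interest stay in the denominator, so the rate can fall well below 100%.

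A reader might also treat the 62% WhatsApp penetration at ages 55 to 64, given in the Introduction, as the share who can be recruited. That does not follow either. Not using WhatsApp is no exclusion criterion; section 2.3.1 asks for the ability to operate a smartphone and allows caregiver help.

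The remaining objections have weight:

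- Patients unable to operate a smartphone even with help are properly ineligible for this intervention and are not recruitment failures. This stands, and the fix respects it.
- The exclusion requires an explicit refusal or unwillingness to share data, so d may be small. This stands; the documents do not show that these are the main reasons for declining.
- The Discussion discloses socio-digital exclusion. It does so as a limit on generalisability, which leaves the outcome's definition unchanged.
- No stated progression rule or sample size depends on this denominator. That limits the consequence, but it also confirms that the recruitment threshold is missing.
- Screening-log detail is commonly left to a full protocol, and the flowchart is not shown. The point here is the stated definition, the stated exclusion and the claim about thresholds, which do not fit together.

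**Conclusion.** The concern holds in a limited form. As defined, the recruitment rate overstates uptake by the factor 1/(1 − d), because refusals specific to a chatbot trial are classed as ineligibility. For assumed d of 0.1 to 0.3 the factor is 1.11 to 1.43; if nobody refuses on these grounds it is 1. The size therefore rests on a quantity that the documents do not give, while the direction follows from sections 2.3.2 and 2.9.1. The rate remains informative about patients who decline for other reasons.

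Two inconsistencies come with it: consent is an eligibility criterion in section 2.3.1 but follows eligibility in section 2.7.1 and Table 1, and the Introduction promises a threshold comparison for recruitment that has no threshold.

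**What to change.** 1. In section 2.9.1, define the denominator as patients who meet all criteria other than consent and the refusal exclusion (digital technology or data sharing). Use the same definition in the Abstract.
2. Count refusal of digital technology, unwillingness to share data and declined consent as not recruited, with a separate count for each reason.
3. Report patients who cannot use a smartphone even with caregiver help separately, as ineligible.
4. State that, for this outcome, consent is an enrolment step and not part of eligibility.
5. In the Introduction, either give a recruitment threshold on this denominator or say that recruitment is estimated descriptively with no threshold.

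The cost is wording and a screening log for patients who are already approached in hospital. No extra patients are needed. The reported rate will be somewhat less favourable. The log should be in place from the start of recruitment, because reasons for refusal are hard to reconstruct later.
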